##### Secondary outcomes

Median duration of antibiotic use, daysProportion of patients receiving only a stat dose of antibioticsProportion of patients receiving <48 h antibioticsProportion of patients receiving intravenous antibioticsMedian duration of intravenous antibiotics, daysProportion of patients with influenza treated with influenza antiviralsProportion of influenza antiviral use occurring in patients with influenzaMedian time to influenza antiviral use, hoursMedian duration of influenza antivirals, daysMedian duration of hospital stay, daysProportion of patients admitted to a side room*Median duration of side room use, days*Median time to isolation or de-isolation, days*Median length of hospital stay, daysMedian turnaround time of respiratory viruses testing, hoursProportion of patients with viruses detectedProportionate mortality in hospital and at 30 days post randomisationProportion admitted to Intensive care or high dependency unitsProportion re-presenting to hospital within 30 daysProportion re-admitted to hospital within 30 daysProportion with prolonged in-patient stay

* A side room is a single-patient room; the use of which is a surrogate measure for isolation for the purpose of infection prevention and control.

Every attempt will be made to recruit patients and deliver the results of POCT prior to antibiotic use however it is understood due to the usual processes of care in hospital that on some occasions antibiotics will be have been administered before POCT is performed or before results are available to clinical teams. Therefore we plan to also undertake a *post hoc* analysis of only those patients where antibiotics were not administered prior to POCT results being available to clinicians.

In view of the deliberately broad inclusion criteria, heterogeneity of treatment effect among different clinical groups is anticipated and therefore subgroup analysis for the primary and certain key secondary outcome measures is planned based on clinical group. Results for antibiotic use (including any use, single dose, and use of less than 48 h duration), duration of antibiotics, admission and length of hospitalisation will be assessed separately for each clinical subgroup.

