The rate of hospitalisation in adults with influenza has been estimated at 5 to 20 per 100,000 overall [12, 13] and may be as high as 1,200 per 100,000 in those over 85 years old [4]. Hospitalisation and death result from the complications of influenza including pneumonia and exacerbation of underlying cardiopulmonary conditions [14]. In adult patients hospitalised with laboratory confirmed influenza, 10–30% are admitted to critical care units and 3–15% die in hospital [15–17] with outcomes being predicted by co-morbidity [17, 18]. Estimates of the burden of influenza virus infection in hospitalised adults have traditionally been based on the incidence of the influenza-like-illness syndrome (ILI, defined as fever of >38 °C and new respiratory symptoms) rather than on laboratory confirmed influenza. ILI has poor sensitivity (around 50%) and specificity (0–63%) for the diagnosis of influenza in hospitalised adults even during periods of peak activity [19–22]. Where estimates of disease burden are based on laboratory confirmed influenza, laboratory testing of patients is based on clinical suspicion of influenza and is generally targeted to patients with respiratory symptoms and fever. However, in addition to acute respiratory presentations, influenza may present as decompensated cardiovascular disease, collapse or diabetic emergencies [23, 24]. For this reason many hospitalised cases of influenza are likely to remain undiagnosed. A recent Canadian study estimated that only around one in 14 ED visits due to influenza virus infection were correctly attributed to influenza [25]. It is likely, therefore, that the burden of influenza and other respiratory viruses amongst hospitalised adults and its economic impact have been under-estimated. In addition to influenza viruses, other respiratory viruses including rhinovirus, respiratory syncytial virus, parainfluenza viruses, human metapneumovirus and coronaviruses, cause acute exacerbations of COPD and asthma as well as other acute respiratory presentations [2], which lead to large numbers of hospitalisations every year and significant burdens upon healthcare systems.

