##### For those randomised to the control group

These patients will be managed using routine clinical care, as per current practice in this large teaching hospital in the United Kingdom, which is a justifiable comparator. Respiratory virus testing using laboratory PCR will be at the discretion of the responsible clinical team.

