##### For both groups

A subgroup of participants may be approached for venous blood sampling and additional nasal/throat swabs to be stored for further study including immunological testing and viral sequencing. All samples will be stored devoid of participant identifiable information to protect participant confidentiality.

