#### Participant timeline

Patients are identified in the AMU and ED by research staff according to eligibility criteria and once written informed consent is obtained they are immediately randomised to the intervention or control group. Those randomised to the intervention group have a nose and throat swab performed immediately by a study doctor or research nurse and this is then tested on the FilmArray machine. Results are available after approximately 1 h and are immediately communicated to the clinical team. Clinical data is then collected retrospectively for both groups. There are no follow up visits for either group.

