#### Statistical methods

This will be performed by a dedicated medical statistician from the University of Southampton independent from the study team. Patients tested with the rapid diagnostic test will be compared with patients treated by routine clinical care using standard descriptive and comparative statistical methods using Prism (GraphPad Software Inc; La Jolla, California) and SPSS (SPSS, Inc; Chicago, Illinois). Summaries of all baseline characteristics will be presented using means and standard deviations, medians and interquartile ranges, or frequencies and percentages, as appropriate. Analysis of the primary outcome will be by intention-to-treat and will compare the proportion of patients receiving antibiotics using the chi-square test for equality of proportions between groups. The effect of group (intervention or control) on the primary outcome will be further assessed using logistic regression to control for demographics (age, sex) and other co-variables. For secondary outcomes the intervention and control groups will be compared using chi-square tests for equality of proportions for binary data (including proportions) and using t-tests and non-parametric equivalent tests for continuous data (e.g. turnaround time) as appropriate.

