## Discussion

We hypothesise that molecular point-of-care testing for respiratory viruses, in adults presenting to hospital with acute respiratory infection, will reduce antibiotic use, improve detection of influenza and use of neuraminidase inhibitors, improve isolation facility use and be safe.

This study has the potential to improve patient care by changing practice and contribute to a health economic analysis. The outcome measures are clinically important to a large number of patients, and also crucial in antimicrobial stewardship and healthcare resource management. As a randomised controlled trial, this study will provide high-quality evidence for the potential use of molecular point-of-care testing for respiratory viruses in hospitalised adults. Beyond this trial, molecular point-of-care testing for common pathogens in select populations, such as in intensive care, or other common illness presentations, such as gastroenteritis, needs to be evaluated to further improve patient care and effectively manage healthcare resources.

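### Two influenza antiviral outcomes depend on influenza status, which is sought in every intervention patient but only at clinicians' discretion in controls, so the planned chi-square tests on them are not valid randomised comparisons

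*Protocol article*

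**What the plan says.** The Secondary outcomes section of the protocol article lists, in consecutive items that run together in the text, "of patients with influenza treated with influenza antiviralsProportion of influenza antiviral use occurring in patients with influenzaMedian time". There are two separate measures here:

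- **Outcome A**: among patients with influenza, the share given an influenza antiviral.
- **Outcome B**: among all influenza antiviral use, the share that falls in patients with influenza.

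The section does not say how influenza status is established.

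The arms differ in how influenza is looked for. Under Participant timeline: "Those randomised to the intervention group have a nose and throat swab performed immediately by a study doctor or research nurse", and the swab is then run on the FilmArray. For controls: "Respiratory virus testing using laboratory PCR will be at the discretion of the responsible clinical team".

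Statistical methods sets the comparison: "For secondary outcomes the intervention and control groups will be compared using chi-square tests for equality of proportions". Influenza antiviral use is a named secondary objective (Study aims and objectives), and the Discussion hypothesises that POCT will "improve detection of influenza and use of neuraminidase inhibitors".

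**The concern.** Being known to have influenza is settled after randomisation, and the intervention is expected to change it. Randomisation does not protect a comparison that depends on it.

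The article supplies the mechanism in its Background. It describes usual practice as one in which "laboratory testing of patients is based on clinical suspicion of influenza and is generally targeted to patients with respiratory symptoms and fever", and concludes: "For this reason many hospitalised cases of influenza are likely to remain undiagnosed". If controls are tested that way, their known influenza cases will be fewer and more typical than those in the intervention arm.

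The two outcomes are affected differently:

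- In A, status defines the denominator. Infected controls who are never tested leave the calculation. Those who remain are mainly the suspected cases, who are also likelier to be treated. This can hide a benefit or make POCT look worse.
- In B, the denominator is antiviral use and status defines the numerator. Infected controls who are treated without a test would not be counted as influenza. This makes control prescribing look less well targeted and favours POCT.

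At stake is a p-value attached to a named objective and hypothesis that could mislead in either direction.

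**Working it through.** The documents give no figure for these outcomes, no influenza prevalence and no control testing rate, so there is no stated result to reproduce. The only planned figure used is the arm size. As a check on it, the unpooled two-proportion formula for 75% v 65% (two-sided 0.05, power 0.80) gives (1.960 + 0.842)² × (0.75×0.25 + 0.65×0.35) / 0.10² = 325.7, matching the stated 326. For the 10% withdrawal allowance, 326/0.9 = 362 and 326×1.1 = 359, both close to the stated 360. Everything below is illustration under assumptions.

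**Outcome A with no true effect.** Assume 360 per arm and 15% truly infected (54 per arm). A share s of cases is clinically suspected. In both arms 70% of suspected and 10% of unsuspected cases are treated. Intervention cases are all detected. Controls are tested with probability t1 if suspected and t0 if not.

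- True rate, both arms = 0.7s + 0.1(1−s)
- Observed control rate = [0.7·s·t1 + 0.1·(1−s)·t0] / [s·t1 + (1−s)·t0]

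For s = 0.5, t1 = 0.9, t0 = 0.1: the true rate is 40%. The control denominator is 27×0.9 + 27×0.1 = 27 instead of 54. Treated among them are 24.3×0.7 + 2.7×0.1 = 17.28, and 17.28/27 = 64%.

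| Suspected share s | True rate (both arms) | Control, tested 90%/10% | Difference | Control, tested 80%/30% | Difference |
|---|---|---|---|---|---|
| 0.3 | 28% | 57.6% | −29.6 | 42.0% | −14.0 |
| 0.5 | 40% | 64.0% | −24.0 | 53.6% | −13.6 |
| 0.7 | 52% | 67.3% | −15.3 | 61.7% | −9.7 |

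Differences are POCT minus control, in percentage points. With equal testing (t1 = t0 = 1) every difference is 0. Prevalence cancels out of the percentages.

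**Outcome A hiding a benefit.** Assume instead that 30% of infected controls are tested and 75% of detected cases are treated in both arms. Intervention: 54 detected, 40.5 treated, 75%. Control: 16.2 detected, 12.15 treated, 75%. Per randomised patient, however, detected-and-treated is 40.5/360 = 11.3% v 12.15/360 = 3.4%. The gap is 0.75 × prevalence × (1 − tested share), which runs from 0.75×0.10×0.50 = 3.8 to 0.75×0.20×0.70 = 10.5 points for prevalence 10–20% and 30–50% tested.

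This gap counts detected-and-treated cases only. If, say, 20 untested controls were also treated empirically and 20–60% of them were infected (4 to 12 patients), treated control infections would be 16.15 to 24.15, or 4.5–6.7% of 360. The gap in treated infection would then be about 6.8 to 4.5 points, not 7.9.

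**Outcome B with no true effect.** Assume 60% of antiviral use truly falls in infected patients in both arms, and a proportion v of treated infected controls is tested. Observed control share = 0.60v.

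| v | POCT | Control | Spurious gain (points) |
|---|---|---|---|
| 0.3 | 60% | 18% | 42 |
| 0.5 | 60% | 30% | 30 |
| 0.7 | 60% | 42% | 18 |
| 0.9 | 60% | 54% | 6 |

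**Full-denominator measures under the first scenario** (s = 0.5, 90%/10% tested, no true effect). Any antiviral use per randomised patient is the same in both arms, because prescribing is the same and testing does not enter. Confirmed influenza plus antiviral is 0.40×54/360 = 6.0% v 17.28/360 = 4.8%. The 1.2-point gap comes from detection alone, so this measure needs a label saying so.

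**The case against.** The strongest reply is that the article condenses a fuller protocol. It does not say that influenza means detected influenza, or that untested treated controls count as non-cases. Swabs may be stored from both arms, and an amendment added a laboratory analysis plan for collected samples. If all controls were tested later by the same method, the bias would go.

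Part of this stands: the counting rule is inferred. If untested treated controls were left out of B instead, the result would rest on a selected subset with a bias of unclear direction. But the stored swabs do not supply status for every control: "A subgroup of participants may be approached for venous blood sampling and additional nasal/throat swabs to be stored for further study". A later analysis plan can change the analysis; it cannot recover the status of patients who were never sampled. The Background account of suspicion-led testing is also general and not a description of this hospital, so the direction for A is likely but not certain.

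A second reply is that the share of patients with viruses detected is listed separately, so better detection would be visible. That helps only in part: it covers all viruses and says nothing about treatment.

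A reader might also infer more than the text supports:

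- That both outcomes use influenza patients as the denominator. Only A does.
- That time to, or duration of, influenza antivirals has the same fault. Neither is stated to be limited to patients with influenza.
- That A would always show no difference. That follows only from assuming equal treatment of detected cases, which ignores any effect of faster results on prescribing.

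**Conclusion.** The point holds for the two quoted proportions. Influenza status is ascertained universally in one arm and selectively in the other, and the article describes no common method, so chi-square tests on A and B are not valid randomised comparisons. The two biases can run in opposite directions.

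Their size is unknown. The shifts of about −10 to −30 points for A and +6 to +42 points for B arise under assumed testing and prescribing rates with no true effect. Other rates would give other values, and equal ascertainment would give none.

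It would be wrong to read this as a threat to the trial's main result. The primary outcome is antibiotic treatment, analysed by intention-to-treat, and does not depend on influenza status. These are two of a long list of secondary outcomes. The change should be made because it is cheap and bears on a named objective and hypothesis, but it is not essential to the trial's validity.

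**What to change.** For between-arm inference, use all randomised patients as the denominator:

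1. The proportion given any influenza antiviral. This needs no influenza status and is a clean randomised contrast.
2. The proportion with confirmed influenza who were also given an antiviral, labelled as the effect of the testing strategy, including its effect on detection.

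Report descriptively by arm, with the number tested and without p-values: outcome A, outcome B, and antiviral use without a positive test, split into tested-negative and untested. The split matters because a single category would again place untested infected controls with non-influenza use.

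Leave the time-to-antiviral outcome as it is on this ground.

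The cost is wording in the outcomes and statistical sections. The data come from the prescribing and laboratory records already being collected. The percentages will be smaller, and measure 2 still partly reflects detection, so it should not be read as a pure effect on prescribing.

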#### Conventional rapid diagnostic tests

Rapid diagnostic tests for influenza, and other respiratory viruses, based on antigen detection in nasal samples have been available for many years but have been diagnostically inaccurate in adults, where sensitivity is around 50% [26, 27]. The poor sensitivity of these antigen-based tests limits their clinical utility and their use has not been associated with a reduction in antibiotic prescribing in adults [28].

The current gold standard diagnostic test for respiratory viruses is laboratory performed polymerase chain reaction (PCR) which is highly sensitive and specific but has turnaround times of at least 24 h and requires specialist laboratory facilities and expertise [29]. New rapid, molecular tests have recently been developed, including the FilmArray Respiratory Panel. These molecular platforms are comparable in accuracy to laboratory PCR, without the need for specialist laboratory support and expertise, and can potentially be used as a point-of-care test (POCT), but the evidence for molecular POCT improving patient outcomes is weak.

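### The planned analysis of patients untreated before the POCT result has no counterpart in controls and is open to selection bias in either direction

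*Protocol article*

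**What the plan says.** Under Secondary outcomes, the protocol article accepts that on some occasions "antibiotics will be have been administered before POCT is performed or before results are available to clinical teams". Its analytical response is a further analysis, planned in advance but labelled *post hoc*, restricted to "only those patients where antibiotics were not administered prior to POCT results being available to clinicians". It gives no cut-off time for the control arm, and does not say whether controls are filtered, kept whole or left out.

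The two arms differ in whether such a result exists at all:

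- **Intervention arm** (Participant timeline): "Those randomised to the intervention group have a nose and throat swab performed immediately by a study doctor or research nurse", straight after randomisation. "Results are available after approximately 1 h and are immediately communicated to the clinical team".
- **Control arm** (For those randomised to the control group): "These patients will be managed using routine clinical care", and "Respiratory virus testing using laboratory PCR will be at the discretion of the responsible clinical team". The background section on conventional tests says that laboratory PCR "has turnaround times of at least 24 h and requires specialist laboratory facilities and expertise".

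The primary outcome is any antibiotic treatment over the hospital stay, capped at 30 days. Statistical methods specifies intention-to-treat for it.

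**The concern.** The rule has two separate faults.

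First, it refers to an event that never happens in controls. Whoever runs the analysis must invent a control-arm counterpart, and the text does not say which.

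Secondly, in the intervention arm the selecting event comes after randomisation, and the reason for exclusion is the outcome itself. A patient dosed between randomisation and result has already counted as treated with antibiotics, and the rule drops that patient. Unless controls lose patients over exactly the same interval, the two sets are no longer comparable, even if the test changes nothing.

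The analysis addresses a question readers will care about: whether the test helps when its result can still influence the first dose. A spurious difference here could be taken for a real effect in the patients best placed to benefit.

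The same sentence also calls the analysis *post hoc* while planning it, which misstates its status.

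**Working it through.** **1. The plan's own figure.** Sample size gives 75% versus 65%, power 0.8 and significance level 0.05. With a two-sided test and unpooled variances:

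n = (1.960 + 0.842)² × (0.75×0.25 + 0.65×0.35) / 0.10² = 7.849 × 0.415 / 0.01 = 325.7, so 326 per group.

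This matches the stated 326. The target of 360 agrees with a 10% allowance (326 × 1.1 = 359; 326 / 0.9 = 363). The 75% rate and the 10-point effect are used below. The article gives no figure for the restricted analysis.

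**2. No true effect, POCT arm filtered, all controls kept.** Let f be the share treated before the POCT result. The article does not give f, so a range is assumed. Everyone removed is a treated patient, so the filtered rate is (0.75 − f)/(1 − f), compared with 0.75 in controls.

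| f (assumed) | POCT arm after filter | Spurious difference | Chance of a false significant benefit |
|---|---|---|---|
| 0.10 | 0.65/0.90 = 0.722 | −2.8 points | 0.13 |
| 0.20 | 0.55/0.80 = 0.688 | −6.2 points | 0.42 |
| 0.30 | 0.45/0.70 = 0.643 | −10.7 points | 0.81 |

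The last column uses the normal approximation at two-sided 0.05, with 360 controls and 360(1 − f) POCT patients. Setting (0.75 − f)/(1 − f) = 0.65 gives f = 0.10/0.35 = 0.286, the share at which the artefact alone equals the planned effect. Here f includes doses given before enrolment, for which the eligibility criteria leave room: recruitment may be up to 24 h after triage or arrival.

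**3. No true effect, controls cut at randomisation, POCT arm cut at the result.** Start from patients untreated at randomisation, and assume 50% of them later receive antibiotics. Let x be the share dosed between randomisation and result. The filtered POCT rate is (0.50 − x)/(1 − x), compared with 0.50.

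- x = 0.05: 0.45/0.95 = 0.474, difference −2.6 points.
- x = 0.10: 0.40/0.90 = 0.444, difference −5.6 points.

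**4. No true effect, controls cut later than the POCT arm**, for example at a PCR result. Write g for the share of controls treated before their cut-off. With f = 0.3 and g = 0.4, the POCT arm is 0.643 and controls are 0.35/0.60 = 0.583, a difference of +6.0 points against the test. A literal reading, in which the result never becomes available so that every treated control is excluded, puts the control rate at 0%, also against the test.

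**5. Both arms cut at randomisation.** Antibiotic status before randomisation cannot depend on allocation, so f is the same in expectation in both arms. With f = 0.3, both rates are 0.643 and the spurious difference is 0, with about 360 × 0.7 = 252 patients per arm.

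**6. Both arms cut at the same time after randomisation.** This is much safer than the written rule but not fully neutral. Suppose ever-use is unchanged but clinicians in the POCT arm tend to wait for the result. With 0.30 treated by the landmark in controls and 0.28 or 0.20 in the POCT arm, the POCT rate is 0.47/0.72 = 0.653 or 0.55/0.80 = 0.688, against 0.643. The bias is +1.0 or +4.5 points against the test.

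**The case against.** **The direction is not fixed.** A reader might infer that the analysis is biased towards the test. The documents do not support that as a general statement. They do not say that controls go unfiltered, and steps 4 to 6 show that other choices give bias against the test or none. This objection stands.

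**The larger figures need strong assumptions.** The result takes about 1 h. In step 3, x = 0.20 would give (0.50 − 0.20)/0.80 = 0.375, a 12.5-point artefact, but it requires 0.20/0.50 = 40% of all later first doses to fall in that short window. Nothing in the article supports such a share, and even x = 0.10 requires 20%. Many doses before the result may instead precede enrolment, and selecting on those in both arms is legitimate. This also stands: the sizes are illustrations.

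**The plan has other handles on early treatment.** A reader might infer that this analysis is its only answer. It is not. Single-dose use, use under 48 h and duration of antibiotics are secondary outcomes that can show early stopping after a result, and the article commits to trying to deliver results before antibiotics are given.

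**It is supplementary, and the article is condensed.** The intention-to-treat analysis is untouched, and a full protocol or analysis plan might state a control cut-off. This limits severity. It does not remove the point, because the article states a selection rule rather than staying silent, and that rule depends on something only one arm has.

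**Conclusion.** The point holds as a fault that should be corrected in a supplementary analysis. As written, the rule does not define a comparison between randomised groups: its selecting event occurs after randomisation and in one arm only, and it selects on the outcome. The bias favours the test if controls are unfiltered or cut earlier than the POCT arm, and runs against it if they are cut later, so an unstated choice by the analyst settles the sign.

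The size is unknown because the article gives no share treated before the result. The illustrations, all under no true effect, run from 2.8 to 10.7 points in favour of the test for f from 0.10 to 0.30 with all controls kept, and from 2.6 to 5.6 points for x from 0.05 to 0.10 with controls cut at randomisation. Apart from the 75% rate, these inputs are assumptions. The primary analysis, its sample size and the conclusion drawn from it do not depend on this rule.

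**What to change.** Define the subset identically in both arms as patients with no antibiotic dose before randomisation, and analyse them in the group to which they were randomised. Describe the analysis as pre-specified and remove the *post hoc* label.

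If a result-time version is still wanted, apply one fixed landmark, the same time after randomisation, to both arms. Label it a sensitivity analysis, since waiting for the result can itself shift who is treated by the landmark.

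The cost is wording only. Outcome data already come from case notes and electronic prescribing systems, on the assumption that dose and randomisation times are recorded there or by the randomisation service. The downside is small: some intervention patients dosed before their result stay in the subset, which slightly dilutes any effect.

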#### Eligibility criteria

##### Inclusion criteria

Aged 18 years or overHas the capacity to give informed, written consent and is able and willing to adhere to the study proceduresIs a patient in Southampton General Hospital’s AMU or EDCan be recruited to the studywithin a 24 h period of first triage by ED staff ORwithin a 24 h period of arrival on AMU (if admitted directly to AMU)
Has an acute respiratory illness* and/or fever >37.5 °CDuration of illness less than or equal to 7 days

*An episode of acute respiratory illness is defined as an acute pulmonary illness (including pneumonia, bronchitis and influenza-like illness) or an acute exacerbation of a chronic respiratory illness (including exacerbation of COPD, asthma or bronchiectasis).

Provisional or suspected clinical diagnoses of acute respiratory illnesses are made by an AMU or ED clinician.

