### Data collection, management and analysis

#### Data collection methods

Clinical and demographic data will be collected at the time of enrolment by research staff from patient paper case notes and electronic medical records. Outcome data will be collected retrospectively by research staff from paper case notes, electronic medical records, electronic prescribing systems, and electronic radiological and laboratory results systems. Final clinical diagnosis will be based on clinical discharge coding and discharge summaries. All source data will be entered into a standardised paper case report form. Patients withdrawn from the study will have no further data collected. Missing data was minimal in the pilot study and is not expected to be a significant issue; the use of multiple imputation will be considered should missing data exceed 10% in the primary outcome.

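### Clinical subgroups are to be assessed separately, which cannot test the heterogeneity the protocol expects, and clinical group is not tied to a diagnosis made before randomisation

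*Protocol article*

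**What the plan says.** Under *Secondary outcomes*, the protocol article notes its broad entry criteria, states that "heterogeneity of treatment effect among different clinical groups is anticipated", and concludes that "subgroup analysis for the primary and certain key secondary outcome measures is planned based on clinical group". The method follows in the next sentence: antibiotic use (any, single dose, under 48 h), "duration of antibiotics, admission and length of hospitalisation will be assessed separately for each clinical subgroup". *Statistical methods* plans a chi-square test and a logistic regression with covariates for the primary outcome. Neither section mentions a treatment-by-group term, and the subgroups are not listed.

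Two diagnoses appear elsewhere:

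- **At entry.** *Inclusion criteria* describes "an acute pulmonary illness (including pneumonia, bronchitis and influenza-like illness) or an acute exacerbation of a chronic respiratory illness" and adds that "Provisional or suspected clinical diagnoses of acute respiratory illnesses are made by an AMU or ED clinician". A patient may also enter on fever above 37.5 °C without a respiratory diagnosis. *Data collection methods* says "Clinical and demographic data will be collected at the time of enrolment by research staff" but does not list a provisional diagnosis as an item.
- **At discharge.** *Data collection methods* says "Final clinical diagnosis will be based on clinical discharge coding and discharge summaries".

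No section says which of the two defines clinical group.

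**The concern.** There are two linked problems.

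**Method and purpose do not match.** The stated reason for the subgroup analysis is that effects may differ. The stated analysis looks at each group on its own. A significant result in one group and a non-significant one in another is not evidence that the effects differ, because small groups will often split that way by chance. The trial is sized for the overall comparison only, so such splits are likely and invite statements that the test works in one illness and not in another.

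**The grouping variable is not fixed in time.** If clinical group were taken from the discharge diagnosis, it would be set after randomisation. By then, under *Interventions*, the test result is in the case notes of the intervention arm and the clinical team has been told of any pathogen. Under *Blinding*, care providers know the allocation. Controls have laboratory PCR only when the clinical team chooses. A viral result could change the final label, and would be available more often in one arm, so patients sharing a label might not be comparable between arms.

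**Working it through.** **1. The plan's own figure.** *Sample size* gives 75% v 65%, power 0.8, significance level 0.05 and 326 per group. With the two-sided unpooled formula:

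n = (1.960 + 0.842)² × (0.75×0.25 + 0.65×0.35) / 0.10² = 7.849 × 0.415 / 0.01 = 325.7, so 326.

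This reproduces, and no stated figure is in dispute. The recruitment target is 360 per group.

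**2. Power of each separate test.** The number and size of the subgroups are not given, so k = 3 to 6 equal groups is an assumption. I use 360 per arm (no withdrawals, which slightly favours the plan) and the same 75% v 65% effect in every group. With m = 360/k per arm and mean proportion 0.70:

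Power = Φ{ [0.10 − 1.96·√(2×0.70×0.30/m)] / √(0.415/m) }

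For k = 3, m = 120: (0.10 − 1.96×0.0592)/0.0588 = −0.271, giving 0.393.
For k = 6, m = 60: (0.10 − 1.96×0.0837)/0.0832 = −0.769, giving 0.221.

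**3. Chance of a mixed pattern with no real heterogeneity.** If each test has power p and the groups are independent, the chance that some are significant and some are not is 1 − p^k − (1 − p)^k. For k = 3: 1 − 0.393³ − 0.607³ = 1 − 0.061 − 0.224 = 0.716.

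| Subgroups | Per arm | Power of each test | Chance of a mixed pattern |
|---|---|---|---|
| 3 | 120 | 39% | 72% |
| 4 | 90 | 31% | 76% |
| 5 | 72 | 26% | 77% |
| 6 | 60 | 22% | 78% |

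**4. If the test has no effect at all.** The chance of at least one false positive on the primary outcome is 1 − 0.95³ = 14% with three groups and 1 − 0.95⁶ = 26% with six.

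**5. What an interaction test could detect.** Assume two equal halves (180 per arm in each), the risk-difference scale, and 75% antibiotic use in controls.

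- Effects of 20 and 0 points: standard error √[(0.1875 + 0.2475 + 2×0.1875)/180] = 0.0671, power Φ(0.20/0.0671 − 1.96) = 85%.
- Effects of 10 and 0 points: standard error √[(0.1875 + 0.2275 + 2×0.1875)/180] = 0.0662, power Φ(0.10/0.0662 − 1.96) = 33%.

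The interaction test answers the right question, but only large differences in effect would be found reliably.

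**6. Relabelling.** Suppose a share s of an intervention-arm group with antibiotic use a is moved to another label, and use among those moved is r. The remainder then has use (a − s·r)/(1 − s). This differs from a unless r = a. The receiving group rises or falls according to whether r is above or below its own rate. The documents give none of s, r or the group-specific rates, so neither the size nor the direction of a distortion can be estimated.

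**The case against.** Only a journal article is shown. Subgroup lists, interaction terms and multiplicity rules are commonly left to a full protocol or analysis plan, so their absence here is not a finding. To say that results will be examined by group does not exclude an interaction term, and the article states no rule for claiming heterogeneity. This has weight, and for that reason the point rests on the method that is stated. The article gives heterogeneity as the purpose and then names separate assessment as the way to address it.

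A reader might infer that the subgroups will be formed from the discharge diagnosis. The documents do not say so. The subgroup sentence refers back to the broad inclusion criteria, which points at least as much to the entry categories, and an entry diagnosis by a clinician is described. It would also be wrong to say that relabelling could happen in one arm only: controls may have PCR at the clinical team's discretion, so the imbalance is one of degree. Nor can a figure be put on the bias, or the six illnesses named at entry be taken as the planned subgroups, since they are introduced as examples.

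What stands is narrower. The choice between entry and discharge diagnosis is open, and the only one with a named data source is the one that the intervention can influence.

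**Conclusion.** The point holds as a modest improvement to the secondary analyses; the intention-to-treat primary comparison is untouched. Separate assessment cannot answer the question the protocol poses. With 3 to 6 equal subgroups and one common 75% v 65% effect, each test has 39% to 22% power, and a misleading mixed pattern would appear in about 72% to 78% of trials. These figures depend on the assumed number and equal size of the groups; unequal groups would leave the smaller ones with less power still.

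The second part is an ambiguity rather than a demonstrated bias. If the entry diagnosis is intended, one sentence settles it. If the discharge diagnosis is intended, the subgroup comparisons lose the protection of randomisation by an unknown amount.

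**What to change.** - Define clinical group by the provisional diagnosis made by the AMU or ED clinician at enrolment, before randomisation. List the groups, with a separate category for patients who entered on fever alone.
- Add a treatment-by-group interaction term to the planned logistic regression for the primary outcome, and a matching term in a suitable model for each of the other subgroup outcomes.
- Report each subgroup effect with its 95% confidence interval, label these results exploratory, and base any statement about heterogeneity on the interaction test.
- Use groups based on the final diagnosis for description only.

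The cost is mainly wording. The article does not confirm that the provisional diagnosis is held as a coded field; if it is not, it would have to be taken from the entry notes. Provisional diagnoses are less accurate than final ones, which may blur real differences between groups, and the interaction test has limited power. The sample size and the primary analysis do not change.
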